#### Assessment aspects

3.5.1

The effectiveness of the photobiomodulation therapy will be assessed by the following protocols:

### Protocol for electromyographic evaluation

1.6

Electromyography will be performed to complement the evaluation of the morphological aspects of the groups. The masseter and temporal muscles will be evaluated using a portable electromyograph (BTS TMJOINT) with wireless electrodes. The participant will be seated with Camper plane parallel to the floor. Three readings will be made on both sides with the muscles at rest, during habitual maximum intercuspation (isometric contraction), and during simulated chewing with Parafilm (isotonic contraction). The signal will be captured for 10 seconds under each condition. The first chewing cycle will be discarded and the subsequent 5 cycles will be collected.

### Protocol for evaluation of salivary cortisol and dopamine levels

1.7

The participants and caregivers will receive verbal and written instructions to avoid any physical activity, the ingestion of substances with alcohol or caffeine, soft drinks, tea, corticoids, and chewing gum in the 24 hours before the collection of the saliva. Saliva samples will be collected using polyester swabs (Salivette, Sarstedt, Germany), which will be refrigerated immediately after collection. The swab will be placed under the tongue and the participant will be instructed to move it around the oral cavity until it becomes soaked with saliva (stimulated saliva). Samples with visible signs of blood will be discarded because of possible contamination by plasma cortisol (Miller et al, 1995). The swabs will be centrifuged at 3500 rpm for 5 minutes. The supernatant will be collected and stored at −40°C. Cortisol will be determined using an enzyme-linked immunosorbent assay (ELISA) (Salimetrics, State College, PA) at room temperature (25°C).

Dopamine will also be determined using an ELIZA kit (Dopamine Research ELISA BA E-5300). The samples will be thawed and centrifuged again. The sample volume will be 25 μL and incubation time will be 60 minutes. The plates will also have controls and standards. The procedure will follow the basic ELISA principle of competition between an untagged antigen and an enzyme-tagged antigen for a particular number of binding sites on the antibody. The analysis will involve reading the absorbance of the solution using a microplate reader set at 450 nm and 630-nm correction filter.

### Analysis of results

1.8

Data will be statistically analyzed using SPSS 24.0 software (IBM Corp., NY), considering an alpha level of 5%, by one of the authors ([name], Applied Statistics Specialist). The exploratory statistics will consist of means, standard deviation, medians, and quartiles. Normality will be tested by Shapiro–Wilk test and Quantilequantile-plot (QQ-plot) analysis. Those variables that do not show normal distribution will be transformed by the natural logarithm (ln).

A general linear model—2-way mixed model analysis of variance (ANOVA)—will be used to test the treatment effect in the observed variance of muscle activity and levels of salivary markers (considered as dependent variables). The effect size (partial Eta squared) and the power of the test for each model will also be obtained. The results of the Mauchley sphericity test and Levene equality of variances will be evaluated as ANOVA premises; when necessary, the Huynh-Feldt correction will be applied.

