**Methods::**

The participants will be 76 children, which will be randomly allocated to a control group, that is group 1, absence of bruxism; group 2, children with bruxism treated with infrared light-emitting diode (LED); and group 3, bruxism treated with occlusal splint. All participants will be submitted to a clinical evaluation to evaluate muscle activity and salivary biomarkers, before and after treatments. Muscle activity will be verified by electromyography of muscles mastication, masseter and temporal, and salivary biomarkers observed will be cortisol and dopamine levels.

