## Material and methods

3

This project was evaluated by the human research ethics committee of University Nove de Julho (certificate of approval: 1.333.636) and clinical trials ID NCT03710174. The sample size was calculated considering α = 0.05 and an 80% power (n = 16 per group), to which 20% will be added to compensate for possible dropouts (n = 19 per group), totaling 76 children and adolescents. Additionally, sample size was calculated for internal validity by using the results of a previous study that evaluated the decrease in signs and symptoms of TMD after occlusal splint therapy (Restrepo et al^[15]^). Considering a mean difference between treatments equal to 2 (SD = 2), 3 groups, power of test of 80%, and an alpha level of 0.05, a minimum of 30 subjects should be included in each group.

The protocol is in accordance with the 2013 SPIRIT (Standard Protocol Items: Recommendations for Interventional Trials) Statement. The SPIRIT checklist can be found as an additional file and Figure 1 is the SPIRIT figure. SPIRIT was developed to provide guidance in the form of a checklist of recommended items to include in a clinical trial protocol, to help improve its content and quality (Fig. 2).

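### Several co-equal outcomes (3 to 14 or more) are each tested at 5% with none named primary, and neither stated sample size is tied to any of them

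*Protocol article*

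**What the plan says.** **Outcomes.** Section 3.5.1 (Assessment aspects) says that effectiveness will be judged through the protocols that follow it: EMG in section 1.6 and salivary markers in section 1.7. On EMG: "The masseter and temporal muscles will be evaluated using a portable electromyograph", and "Three readings will be made on both sides with the muscles at rest, during habitual maximum intercuspation (isometric contraction), and during simulated chewing". On saliva, the abstract says: "salivary biomarkers observed will be cortisol and dopamine levels".

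**Analysis.** Section 1.8 (Analysis of results) works at a single level, "considering an alpha level of 5" per cent. It uses a two-way mixed ANOVA to test the treatment effect on "muscle activity and levels of salivary markers (considered as dependent variables"), and adds that "the power of the test for each model will also be obtained". So there is more than one model, but their number is not given and the outcomes are not ranked.

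**Sample size.** Section 3 (Material and methods) gives two calculations, both at 80% power and alpha 0.05. The first gives 16 per group, raised to 19 for dropout and 76 in total, with no outcome, effect size or SD. The second is introduced as additional. It takes a difference of 2 (SD 2) with three groups from a study that "evaluated the decrease in signs and symptoms of TMD after occlusal splint therapy", and asks for at least 30 per group.

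**Timing.** Section 1.5 assesses the LED groups immediately after the session and one week later, and the splint group after one month of use.

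**The concern.** With several equal outcomes at an undivided 5%, nothing in the article says which result decides whether LED works. A significant finding in one muscle, side, condition or marker could be reported as the treatment effect. Because the handling of the EMG channels is also left open, the number of tests could be settled after the data are seen.

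The stated power has a related problem. Power belongs to a particular outcome, contrast and effect size. One calculation names none of these. The other takes its effect from an endpoint that the article does not list among its assessments. A reader therefore cannot say for which of the trial's own hypotheses the 80% holds.

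**Working it through.** **Inputs.** From section 1.6: 2 muscles, 2 sides, 3 conditions. From the abstract and section 1.7: 2 salivary markers. From section 1.8: 5% per model. From section 3: 16, 19 and 76; and difference 2, SD 2, 3 groups, 80% power, 30 per group.

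**Step 1: the plan's own sample sizes.** For two means at two-sided 5% and 80% power,

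n per group = 2 × (1.960 + 0.842)² × (SD / difference)² = 2 × 7.85 × (2/2)² = 15.7, so 16.

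A 1 SD effect therefore yields the article's first figure, 16, although the article attaches no effect size to it. Then 16 × 1.2 = 19.2, stated as 19, and 19 × 4 = 76. That total fits four groups, whereas section 1.3.1 lists three (19 × 3 = 57).

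The second figure, 30, does not follow from the inputs given with it:

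| Method, difference 2, SD 2, 80% power | n per group |
|---|---|
| Two-sample t test | 17 |
| Bonferroni over 3 pairwise comparisons | 21 (normal), 23 (t) |
| One-way ANOVA, 3 groups, means −1, 0, 1 | 21 |
| One-way ANOVA, 3 groups, means 0, 0, 2 | 16 |
| Non-standard: SD multiplied by √2 | 32 |

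Also, 3 × 30 = 90, which exceeds the planned 76.

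**Step 2: how many tests.** The article does not say how EMG readings are combined, so three counts are shown:

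- one muscle-activity variable: 1 + 2 = 3
- sides averaged: 2 × 3 + 2 = 8
- every muscle, side and condition separate: 2 × 2 × 3 + 2 = 14

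The count would exceed 14 if several EMG parameters, or the morphological and psychosocial evaluations mentioned in section 1.5, were also tested. The article does not say so.

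**Step 3: family-wise error.** With m independent tests at 5% it is 1 − 0.95^m. With a common correlation ρ between normal test statistics it is

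1 − ∫ φ(z) [Φ((c − √ρ z)/√(1−ρ)) − Φ((−c − √ρ z)/√(1−ρ))]^m dz, with c = 1.960.

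| m | independent | ρ = 0.3 | ρ = 0.5 | ρ = 0.7 |
|---|---|---|---|---|
| 3 | 14.3% | 13.6% | 12.5% | 10.9% |
| 8 | 33.7% | 30.0% | 25.0% | 19.1% |
| 14 | 51.2% | 43.8% | 34.8% | 24.9% |

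The article gives no correlations, so the values of ρ are assumptions.

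**Step 4: what one primary outcome would do.** Suppose a 1 SD effect on that outcome, 16 analysed per group and one two-group comparison at two-sided 5%. Power is Φ(√(16/2) × 1 − 1.960) = Φ(0.868) = 80.7%, or 78.1% by the t distribution. If instead 14 outcomes shared the 5% by Bonferroni, power per outcome at the same effect would be 46.6% with 16 per group and 56.7% with 19, and 80% would need 29 per group (normal approximation).

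**The case against.** The strongest reply is that this is a condensed article. An analysis plan may exist, and a multiplicity method or the reduction of EMG channels is commonly placed there. A 5% level is conventional and not an error in itself. This stands as far as the adjustment method goes: its absence here is not a fault.

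A reader might also infer that at least 14 ANOVAs are planned. The documents do not support that as a floor. Section 1.6 describes how EMG is recorded, not which recordings become endpoints, and section 1.8 gives no number of models. At the low count of 3 the inflation is moderate, 11% to 14% in the table above, so the 51% figure must not be quoted alone.

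A reader might further infer that the trial does not measure TMD signs and symptoms at all. That is too strong: section 1.5 mentions morphological and psychosocial evaluations without listing them. What can be said is that no such outcome is described. Nor do the documents show the scale on which the 2 and the SD of 2 were measured.

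Finally, it would be wrong to call the TMD-based calculation the trial's only one. The planned total of 76 comes from the 16-per-group calculation.

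What the reply does not remove is the gap in section 3. An unseen analysis plan cannot make a sample size already published without an outcome, or with another study's endpoint, apply to EMG or saliva. Nor does obtaining power for each model at the analysis stage: that does not show what the trial was designed to detect.

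**Conclusion.** The point holds in this form. Between 3 and 14 or more outcomes stand as equals, each at 5%, and the article designates none as primary. If the tests are independent, the family-wise error is about 14% for 3, 34% for 8 and 51% for 14. It is lower under positive correlation, for example 25% for 14 tests at ρ = 0.7. These figures assume that all null hypotheses are true, that each outcome has one test, and that any single positive result could be claimed.

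Both statements of 80% power lack a link to EMG, cortisol or dopamine. The two resulting sizes, 16 (19 with dropout) and 30 per group, also disagree. This does not show that the trial is underpowered for any outcome. It shows that the power for its outcomes is unknown from the article.

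**What to change.** 1. **Name one primary outcome.** State one muscle, one recording condition, how the two sides are combined, one between-group contrast and one assessment time. Test it at 5%. Which muscle and condition to choose is for the investigators.
2. **Reconcile the schedules first.** Section 1.5 places the LED assessments immediately and at one week and the splint assessment after one month, so no common time exists at present. Those passages must be reconciled so that the contrast is made at a defined time.
3. **Label all other variables secondary.** Either interpret them as supportive or apply a stated multiplicity adjustment, and say how many EMG variables there are.
4. **Restate the power for the primary outcome** as an explicit assumption in SD units. For example, 1 SD with 16 analysed per group gives about 78% to 81% for one two-group comparison at two-sided 5%. Justify the assumption for the chosen variable and do not present the TMD data as its support.
5. **Reconcile 16/19 with 30 per group**, and both with the total of 76 and the number of groups.

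Items 1, 3 and 4 are wording, best settled before any outcome data are examined. Items 2 and 5 need design decisions and may change when children are assessed or how many are enrolled. The price is less scope to claim efficacy from secondary variables, and a power statement that is openly conditional on an assumed effect.

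### Normality checks on the trial data choose the raw or ln scale for each variable, so the effect measure, and possibly the group-by-time result, depend on chance and sample size

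*Protocol article*

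**What the plan says.** Section 1.8, Analysis of results, sets out this sequence:

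- Check: "Normality will be tested by Shapiro–Wilk test and Quantilequantile-plot (QQ-plot) analysis".
- Consequence: "Those variables that do not show normal distribution will be transformed by the natural logarithm (ln".
- Model: a "2-way mixed model analysis of variance (ANOVA", applied to "muscle activity and levels of salivary markers (considered as dependent variables".
- Software: "Data will be statistically analyzed using SPSS 24.0 software".

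The Abstract (Methods) says that the trial will "evaluate muscle activity and salivary biomarkers, before and after treatments", so each outcome is a repeated measurement.

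The section assigns no outcome a scale in advance. It does not say what happens when the test and the plot disagree, or whether a variable is a whole outcome or one visit of it. It lists sphericity and equality of variances as model premises, but attaches normality to the variables and does not mention residuals.

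**The concern.** This is a rule that the article states, not a detail left for a later plan. Three things follow from it.

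1. The scale is settled after the data are seen. On the raw scale the effect is a difference of means. On ln it is a ratio of geometric means. Cortisol, dopamine and the EMG conditions could end up with different measures for no scientific reason.
2. The check looks at the wrong object. ANOVA needs approximately normal residuals. If the groups are pooled for the check, a genuine level difference between children with and without bruxism can itself make a variable look non-normal.
3. A group-by-time interaction depends on scale when groups start at different levels. Group 1 is defined by the absence of bruxism, so its level may differ from that of groups 2 and 3.

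A further risk depends on the reading of the text. A repeated-measures GLM in SPSS takes each visit as its own column. If variables means columns, one visit could be logged and the other left raw.

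**Working it through.** The plan states no figure on this point, so there is none to reproduce.

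**Inputs from the article.** The rule, the model and the 5% level come from section 1.8. The size of 19 per group comes from Material and methods; three groups give 3 × 19 = 57. The same section states a total of 76, which is 4 × 19, and elsewhere 30 per group.

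**Assumptions, none of them in the article.** Data are log-normal with log-SD 0.2 to 0.7 and correlation 0.5 to 0.8 between visits. Shapiro–Wilk is judged at 0.05. The QQ-plot judgement cannot be simulated and is left out.

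**Step 1. How often ln is chosen at a given visit** (2,500 runs per setting)

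| log-SD | n = 19 | n = 57 |
|---|---|---|
| 0 (normal data) | about 5% | 4–5% |
| 0.2 | 12–14% | 32–34% |
| 0.3 | 23–24% | 63–65% |
| 0.5 | 49–50% | 95–96% |

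The same distribution gets a different effect measure according to how many children are tested.

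**Step 2. Why the scale matters for group-by-time.** Take a level of 5 in groups 2 and 3, a level 30% lower in group 1 (5 × 0.7 = 3.5), and a 20% fall in all groups.

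- Raw changes: 5 × 0.8 − 5 = −1.0 and 3.5 × 0.8 − 3.5 = −0.7. They differ by 0.3.
- ln changes: ln 0.8 = −0.223 in every group. They differ by 0.

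The interaction exists on one scale and not on the other. In simulation (3 × 19, median 5, log-SD 0.2–0.3, correlation 0.5–0.7), choosing the scale once per outcome gives about 6–20% significant group-by-time tests. With ln fixed the rate is about 5–6%. These rates count against the null of equal ratios; on the raw scale the difference of 0.3 is real. The point is that the data pick which question is answered.

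**Step 3. If the decision were made visit by visit.** Suppose nothing changes over time, with baseline raw and follow-up on ln.

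- Level 5: ln 5 − 5 = 1.609 − 5 = −3.391.
- Level 3.5: ln 3.5 − 3.5 = 1.253 − 3.5 = −2.247.

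A large spurious time effect appears in both. The spurious changes differ by 1.144 between the two levels, and by nothing if levels are equal. Simulation (3 × 19, log-SD 0.2–0.3, correlation 0.6, 4,000 runs per setting, no true effect) agrees:

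- Scales are mixed in 31–41% of runs.
- The time effect is falsely significant in 34–44% of all runs and in every mixed run.
- Group-by-time error is near 5% with equal group levels. With group 1 30% lower it is 6–8% at median 1 unit and 36–37% at median 5 units (31–41% over correlations 0.5–0.7).
- With ln fixed in advance, group-by-time error is 4.3–5.5% and time error 4.4–5.3%.

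**Step 4. How often the two visits would disagree.** With three groups pooled (n = 57) and correlation 0.5, it is about 42–45% at log-SD 0.3, 8% at 0.5 and 0.4% at 0.7. With 76 pooled it is 34% at log-SD 0.3 and 1.5% at 0.5. The figure depends heavily on the assumptions.

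**The case against.** **The mixed-scale reading is not the natural one.** The next paragraph of section 1.8 uses the word variables for whole outcomes, "muscle activity and levels of salivary markers (considered as dependent variables". On that reading cortisol is logged at every visit or at none. This stands. A reader might infer that baseline and follow-up will be put on different scales. The text only fails to rule it out.

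**On the whole-outcome reading the test keeps its level.** With no change over time and the decision made once per outcome, group-by-time error is 4.7–5.6% and time error 4.4–5.4%, practically the same as with ln fixed. This stands for that setting. It does not cover a change shared by all groups combined with unequal levels, where step 2 shows that the answer depends on the scale.

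**Even mixed scales need not invalidate the group-by-time test.** With two arms of 19 at equal baseline levels, the error is 4.0–4.7% overall and 4.3–5.0% in mixed runs. This stands for type I error, and it bears most on LED against splint. The estimate in such a run would still have no usable unit.

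**Shapiro–Wilk is not the only trigger, and pooling is not stated.** Both are true. The QQ-plot adds a judgement made on the same data, with no rule for disagreement, so it does not repair the rule. A condensed article may leave the grouping of the check to a fuller document. Letting the check select the scale is stated outright.

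**Conclusion.** The point holds on any reading in this form: the effect measure is chosen from the trial data, by checks on variables rather than residuals, and can vary with chance, sample size and outcome. Where group 1 differs in level, the group-by-time conclusion can depend on that choice. The size shown is about 6–20% against about 5–6%, under an assumed 30% lower level in group 1, a shared 20% fall, median 5 and log-SD 0.2–0.3.

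Different scales at two visits of one outcome are a possibility left open, not something the plan prescribes. If it happened, the time effect and the effect estimate would be uninterpretable. A reader might go further and call every group-by-time test under the rule invalid. The evidence does not support that: with equal group levels the error stays near 5%.

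The article gives no distribution, correlation or level for any outcome, so every percentage here is conditional on the assumptions. The change should be made before analysis because it is cheap and the rule governs all the outcomes.

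**What to change.** Replace the two sentences on normality and transformation with a rule that does the following:

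- Names the scale of each outcome in advance: ln for salivary cortisol and dopamine, and a stated scale for each EMG parameter. Section 1.6 describes the recordings but names no derived parameter, so parameter and scale should be fixed together.
- Uses that scale at every time point.
- Reports effects on that scale with 95% confidence intervals, as ratios of geometric means where ln is used.
- Checks QQ-plots of model residuals, as a diagnostic only.
- Gives a prespecified analysis on the other scale as sensitivity only.
- Deletes the normality-test trigger.

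The cost is about two sentences of analysis wording and no extra data. The downside is that results on ln are read as ratios rather than as differences in the original units.

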#### Groups:

1.3.1

The participants will be randomly allocated to the following groups:

Group 1: control—absence of bruxism.Group 2: bruxism treated with infrared LED.Group 3: bruxism treated with occlusal splint.

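### The mixed ANOVA named as the test of treatment effect appears to include the bruxism-free group, so its group-by-time F does not isolate LED versus splint

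*Protocol article*

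**What the plan says.** Under Analysis of results, the protocol article names a single inferential procedure: "A general linear model—2-way mixed model analysis of variance (ANOVA)—will be used to test the treatment effect", with muscle activity and the salivary markers as dependent variables. It adds: "The effect size (partial Eta squared) and the power of the test for each model will also be obtained". It does not name the factors, the term that decides, or a contrast between groups.

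The section headed Groups lists three groups, the first being "Group 1: control—absence of bruxism"; the other two are bruxism treated with infrared LED and bruxism treated with an occlusal splint. It says that participants are randomly allocated to all three. The Methods part of the Abstract has all participants assessed before and after treatment. Nothing takes Group 1 out of the model. Its inclusion is therefore a reading of these sections together, not an explicit statement.

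The Photobiomodulation treatment protocol section differs from this list. It describes a red LED group, an infrared LED group and a splint group numbered 4. LED is assessed immediately and one week after the session, and splint after one month of use.

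**The concern.** A child without bruxism cannot be allocated to a bruxism arm, nor the reverse. Under the three-group list, LED versus splint is thus the only comparison that randomisation can protect. A three-level group factor combines it with a comparison of diseased and healthy children.

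The group-by-time F asks whether all three groups change alike. It rejects if both bruxism arms improve to the same degree and healthy children stay put. It also rejects if splint works and LED does nothing beyond what healthy children show. Either result could be reported as a significant treatment effect in a trial meant to evaluate LED. Partial eta squared would not help, since it has no direction and does not say which groups differ.

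**Working it through.** **Inputs from the document.** 19 per group ("20% will be added to compensate for possible dropouts (n = 19 per group), totaling 76 children and adolescents") and alpha 0.05, taken as two-sided. The planning values are "Considering a mean difference between treatments equal to 2 (SD = 2), 3 groups, power of test of 80%, and an alpha level of 0.05", so the planning difference is 2/2 = 1 SD. As a check on that scale, the usual two-group formula gives 2 × (1.960 + 0.842)² / 1² = 15.7, or 16 per group. This agrees with the first stated size ("The sample size was calculated considering α = 0.05 and an 80% power (n = 16 per group"), although no effect size is given with it. It does not give the 30 per group stated next, which is a separate problem and does not decide this point.

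**Assumptions.** The document gives no pre/post correlation r, so 0.3, 0.5 and 0.7 are used. A change of 0.8 SD is assumed, with 1 SD alongside. Data are normal with equal SDs, one measurement before and one after.

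**Step 1: the group-by-time F.** With two time points this F equals a one-way ANOVA on the change. In SD units the variance of the change is 2(1 − r), that is 1.4, 1.0 and 0.6. The noncentrality is λ = n Σ(mᵢ − m̄)² / [2(1 − r)], with 2 and 54 degrees of freedom and critical value 3.168.

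Let LED and splint both change by 0.8 SD and healthy children by 0. The mean is 0.533 and the sum of squares is 0.533² + 2 × 0.267² = 0.427. Then 19 × 0.427 = 8.11. If only splint changes, with LED equal to healthy, the sum of squares is the same, so both situations share these results:

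| r | λ at 0.8 SD | F significant, 0.8 SD | F significant, 1 SD |
|---|---|---|---|
| 0.3 | 5.79 | 54% | 75% |
| 0.5 | 8.11 | 70% | 88% |
| 0.7 | 13.51 | 90% | 98.5% |

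A 20,000-run simulation at r = 0.5 with an equal 1 SD change in both arms also gave 88% for the F, while a baseline-adjusted LED-versus-splint test stayed at 5%. With 25 per group (76/3), the 1 SD figure at r = 0.5 is 96%.

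**Step 2: the LED-versus-splint contrast.** The residual variance is 2(1 − r) for change scores and 1 − r² for ANCOVA. Their ratio is (1 − r²) / [2(1 − r)] = (1 + r)/2, which never exceeds 1. For a true difference of 0.8 SD, the noncentrality is 0.8 / √(variance × 2/19), with 36 degrees of freedom (change) or 35 (ANCOVA):

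| r | Ratio | Power, change score | Power, ANCOVA |
|---|---|---|---|
| 0.3 | 0.65 | 53% | 71% |
| 0.5 | 0.75 | 67% | 79% |
| 0.7 | 0.85 | 87% | 92% |

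On the planning scale (SD 2, difference 2), the 95% confidence interval for the ANCOVA contrast has a half-width of 1.26, 1.14 and 0.94.

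**Step 3: ANCOVA against the three-group F.** For an LED-splint difference of 2 (SD 2) at r = 0.5, ANCOVA has 93% power. The F has 88% if healthy children change like the splint arm, and 77% if they change midway between the arms. The order can reverse. At r = 0.9, with a difference of 1 and healthy equal to splint, the F has 94.4% against 93.0%. If LED changes by 3, splint by 1 and healthy by 0 at r = 0.5, the F rejects in 98.9% against 93.3%, partly because of the gap between bruxism and healthy children.

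**The case against.** The article does not say that Group 1 is in the model, that an omnibus F decides, or which term counts. It condenses a fuller plan, which may hold contrasts and intervals. That stands in part: a missing interval or follow-up contrast is not counted here as a fault. What remains is that the article states which test answers the treatment question, and on its natural reading that test does not isolate the randomised comparison.

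A reader might infer that the test is likely to be positive with no treatment effect at all. That would hold for the group main effect: with bruxism children 0.8 SD above healthy children at both times and no change anywhere, it is significant in about 82% of trials at r = 0.5. The article never names that term as deciding, however, and group-by-time stays at 5% when nobody changes.

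An equal change in both bruxism arms is also not a type I error of the F, because the groups do differ in change. The Aim names no comparator, and both treatments might truly work. That is correct. The F still cannot say whether LED contributed. Healthy children do not control for natural course or regression to the mean in bruxism.

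Finally, the equivalence with a change-score analysis needs two time points. The LED assessments, and the planned sphericity check, suggest there may be more.

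**Conclusion.** The point holds as a problem of which comparison is tested. If Group 1 is in the model, a significant group-by-time F does not separate LED from splint, nor show that LED did more than nothing. The size is 54% to 90% significant results for a 0.8 SD change with 19 per group. It rests on an assumed r of 0.3 to 0.7, an assumed change, and one before and one after measurement.

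The gain in precision is a second, smaller argument. Between two randomised arms a change-score comparison is valid, and ANCOVA is at least as precise apart from one degree of freedom. The gain shrinks as r rises. A general claim that ANCOVA has more power than the three-group F is not supported, as Step 3 shows.

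The planned power of the test, if it means power computed from the observed result, is for a given design a function of the p-value. It adds nothing, but this is minor.

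**What to change.** 1. Reconcile the Groups section with the Photobiomodulation treatment protocol section, on the groups and their numbering and on the assessment times, so that the compared arms share a comparable final assessment. Until then an analysis of the final value would set LED at one week against splint after one month. Correct the statement that Group 1 is randomly allocated.
2. Name as the deciding analysis an ANCOVA of the final value (ln scale where used) on arm and baseline, in the randomised bruxism children only, reporting LED minus splint with its 95% confidence interval.
3. Keep Group 1 for a secondary reference comparison, labelled as non-randomised.
4. Report the interval in place of the power of each model.
5. State that, with no untreated or sham bruxism arm, the result is LED relative to splint. A difference near zero would not show whether either treatment works.

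Items 2 to 5 cost only wording and use baseline data already planned. Item 1 is more than wording, because it may change when children are assessed. All should be settled before outcome data are examined.

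### The power figure planned for each fitted ANOVA is observed power: it re-expresses the p-value and is not the power of the design

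*Protocol article*

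**What the plan says.** The protocol article, under Analysis of results, plans a two-way mixed ANOVA at a 5% alpha level. The software is fixed: "Data will be statistically analyzed using SPSS 24.0 software". The model "will be used to test the treatment effect in the observed variance of muscle activity and levels of salivary markers". Two further outputs are then added: "The effect size (partial Eta squared) and the power of the test for each model will also be obtained". No effect is named at which this power is to be evaluated, and no use for it is stated.

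Design power is treated separately, under Material and methods. One calculation reads "The sample size was calculated considering α = 0.05 and an 80% power (n = 16 per group" and gives no effect size. A second, based on a study of signs and symptoms of TMD after splint therapy, takes a difference of 2 with SD 2, three groups and 80% power, and concludes that "a minimum of 30 subjects should be included in each group".

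**The concern.** The article uses power for two different things. In the sample size paragraph it is a property of the design, fixed before any data exist by an assumed difference, an SD and a sample size. In the analysis section it is obtained once per fitted model, beside the sample effect size, so it can rest only on the estimated effect. That is what SPSS calls observed power.

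Observed power carries no information beyond the p-value. Because both quantities go by the same name, the natural comparison is with the protocol's own 80%. A null result would then seem to come from a test that was too weak, even where the design had ample power. With several EMG conditions and two salivary markers, many such figures would be produced.

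**Working it through.** **Inputs.** Alpha is 0.05 (Analysis of results). The sample sizes are 16, 19 and 30 per group, and the planning values are difference 2 and SD 2 (Material and methods). The article does not settle the degrees of freedom. It lists three groups but describes a fourth in the treatment section, and it gives the LED groups three assessments (initial, immediately after the session, 1 week later). Several layouts were therefore tried.

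**The plan's own figures.** For two means, n = 2 × (1.960 + 0.842)² × (SD/difference)² = 2 × 7.85 × 1 = 15.7, so 16 per group, with power 80.7% by the normal approximation. This matches the stated 16 if that calculation also assumed a 1 SD difference, which the article does not say. The stated 30 per group was not reproduced: the same inputs gave 16 to 23 across a two-group comparison, a Bonferroni version and a three-group ANOVA. The present point does not depend on that.

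**Formula.** Let F be the observed statistic with df1 and df2, and Fc the 5% critical value. Then

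observed power = P(F′(df1, df2, λ) > Fc), with λ = df1 × F,

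where F′ is noncentral F. Once df1, df2 and alpha are fixed, F determines both the p-value and λ. Observed power is therefore a strictly decreasing function of p and of nothing else.

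**Worked case: three groups of 19, df 2 and 54, Fc = 3.168.**

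| p | F | λ = 2F | observed power |
|---|---|---|---|
| 0.01 | 5.021 | 10.04 | 79% |
| 0.05 | 3.168 | 6.34 | 58% |
| 0.10 | 2.404 | 4.81 | 46% |
| 0.20 | 1.658 | 3.32 | 33% |
| 0.50 | 0.702 | 1.40 | 16% |

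**Ceiling for a non-significant test.** Setting F = Fc gives the value at p = 0.05, which no test with p > 0.05 can exceed.

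| Layout (illustrative) | df1, df2 | λ = df1 × Fc | ceiling | p needed for 80% |
|---|---|---|---|---|
| 2 groups of 19 | 1, 36 | 4.11 | 51% | 0.007 |
| 3 groups of 19 | 2, 54 | 6.34 | 58% | 0.009 |
| 4 groups of 19 | 3, 72 | 8.20 | 64% | 0.013 |
| 3 groups × 3 times | 4, 108 | 9.82 | 69% | 0.018 |
| 4 groups × 3 times | 6, 144 | 12.97 | 75.5% | 0.033 |

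The ceiling rises with df1. It would pass 80% at df1 = 8 (81% with df 8 and 200), which no layout described in the article produces.

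**Contrast with design power.** For three groups with means 0, 1, 2 and SD 2, λ = n × [(0−1)² + (1−1)² + (2−1)²]/2² = n/2. This gives power 68.6% at n = 16, 77.0% at n = 19 and 93.6% at n = 30, whatever the data turn out to be. In 20,000 simulated trials at n = 30, the highest observed power among non-significant results was 58% and the median was 46%. A design with 93.6% power would thus show about half that figure whenever its test was not significant.

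**Scatter.** With 16 per group and one of three groups 1 SD away, true power is 81%. The 5th to 95th percentiles of observed power run from 33% to nearly 100%, and about 15% of trials fall within 5 points of the truth. This scenario joins the 16 of one calculation to the 1 SD difference of the other and assumes one pattern of means, so it is an illustration only.

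**The case against.** The strongest reply is that the article says only that the power will be obtained. It does not say that it will be reported as design power or used to explain null results. That stands: the misreading is a foreseeable risk, not a stated intention. It does not rescue the clause, because a quantity listed in the analysis plan beside an effect size is evidently meant to be used, and with no assumed effect named no other workable reading is apparent.

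Three stronger readings are tempting and are not supported.

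- A reader might infer that every non-significant result must show power under about 51% to 58%. That holds for between-group tests of two or three groups. The planned mixed ANOVA can produce interaction tests with df1 of 4 or 6, where the ceiling is 69% or 75.5%.
- A reader might infer that chance positives would generally be endorsed by high power. Under the null, p is uniform, and 80% is reached only at p of about 0.0097 (df 2, 45) or 0.0070 (df 1, 30). So 0.0097/0.05 = 19% or 0.0070/0.05 = 14% of chance positives would show 80% or more. The share is a majority only at high df1 (0.0325/0.05 = 65% at df 6, 144).
- A reader might count the absence of confidence intervals as a defect. This is a condensed article, and intervals may be specified in a document not shown. The defect is the commitment to a mislabelled quantity.

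**Conclusion.** The point holds and is minor. The planned power figure re-expresses each p-value and is not the design power of the sample size paragraph. In every layout checked, a test with p > 0.05 shows a value below the protocol's 80%: at most 51% for df1 = 1, 58% for df1 = 2, and 64% to 75.5% for df1 from 3 to 6.

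This rests on two assumptions. First, the figure is SPSS observed power, an inference from the wording and the software. Second, the degrees of freedom lie in the range tried, because the article leaves the number of groups and assessments unclear. A Huynh-Feldt correction would change the degrees of freedom but not the one-to-one relation to the corrected p-value.

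The clause does not make the analysis invalid. The F tests, their type I error, the estimates and the sample size are untouched. Only the interpretation is at risk, chiefly of null results.

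**What to change.** In Analysis of results, end the sentence on effect size after partial eta squared and delete its power clause. In its place, state that each outcome will be given with the estimated between-group treatment difference and its 95% confidence interval from the same model. The text should say which assessments the difference compares, since the LED and splint arms are described with different follow-up times. Where a variable was ln-transformed, back-transform the interval, so that it reads as a ratio of geometric means.

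Quote power only as the a priori figure, with the difference and SD it assumes.

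Do not judge EMG, cortisol or dopamine intervals against the difference of 2 in the sample size paragraph. It comes from TMD signs and symptoms and has no meaning on those scales. Interpret each interval on the outcome's own scale or in SD units.

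The cost is one sentence. No new data are needed and the model does not change.
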